#### Emergency Unblinding

To optimize study quality, emergency unblinding will only occur when knowledge of the intervention is essential for participant care, as determined by the principal investigator. In the case of emergency unblinding, the timing, reason for doing so, and personnel involved will be recorded in the case report form, while blinding is maintained by as many other study personnel as possible.

### Outcome Measures

#### Primary Outcome

The primary outcome of this pilot trial is to determine the feasibility of a large-scale multicenter trial. Feasibility outcomes will include the following variables, with all thresholds listed in parentheses:

Recruitment success (with the specific aim of recruiting all necessary patients within the first year of the trial period).Adequate consent rate (>30% of eligible patients consent to participate in the study).Percentage of patients who complete all medication and psychotherapy visits (ie, intervention adherence; >90%).Percentage of patients who withdraw from the study (eg, due to side effects or other reasons; <20%).Percentage of patients with incomplete pain intensity and pain interference data at 1 month and stated or ascribed reason (eg, withdrawal due to side effects, loss of follow-up, or missing data; <10%).Rate of adverse outcomes (ie, 0 serious adverse events).

Based on the result for each primary feasibility outcome, we will determine whether the definitive study is feasible as proposed (ie, all feasibility targets are met), feasible with protocol modifications (modifications specified), or not feasible because feasibility targets could not be met even with protocol modifications. These cutoffs, identified in the parentheses above, will help determine whether protocol changes are required before proceeding with a definitive trial.

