#### Hypothesis

In line with the primary aim of this study, this pilot study will prove to be feasible for a large-scale clinical trial. We expect that we will be able to successfully meet our recruitment target (30 participants) within the 1-year time frame of the study and expect this study withdrawal rate to be less than 10% (3/30 patients). Feasibility of this study will be determined by the following set variables and cutoff percentages; recruitment success with the specific aim to recruit all necessary patients within the first year of the trial period, adequate consent rate (30/100, >30% of eligible patients consent to participate in the study), intervention adherence as define by the percentage of patients who complete all medication and psychotherapy visits (27/30, >90%), percentage of patients who withdraw from the study (ie, due to side effects; 6/30, <20%), percentage of patients with incomplete pain intensity and pain interference data at 1 month, (eg, withdrawal due to side effects, loss to follow up, or missing data; 3/30, <10%), and rate of adverse outcomes. We do not foresee any issues arising with the protocol of the study or the delivery of each arm.

While not powered to examine these effects, we hypothesize that patients allocated to the combination ketamine and CBT/MM arm of this study will have the greatest reduction in pain intensity and pain interference.

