#### Secondary Outcome

The secondary outcomes chosen for the definitive trial follow consensus recommendations of core domains that should be addressed in studies examining chronic pain. Information will be collected in these domains as part of the pilot trial using survey-based outcome assessments, either in person during study visits or over the telephone by trained research personnel. The following pain score questionnaires will be used:

Pain intensity on an 11-point (0-10) Numeric Rating Scale.Pain interference on the Patient-Reported Outcomes Measurement Information System (PROMIS-PI) scale.Catastrophic thinking about pain, as measured by the Pain Catastrophizing Scale (PCS).Features of depression, as measured by the Patient Health Questionnaire-9 (PHQ-9).Features of anxiety, as measured by the Generalized Anxiety Disorder-7 (GAD-7).Patient Global Impression of Change Scale (PGIC).

Secondary clinical outcomes will include changes relative to baseline assessment in pain intensity and pain interference at week 20 (4 weeks post-completion of treatment; Figure 1). Scores for all outcomes at weeks 2, 7, 12, 16, and 20 will be compared to baseline scores to assess any progressive additive effects between the treatments. For any patients who withdraw before week 20, their last documented responses will be used as a comparison against baseline data. Patients will be allowed to adjust the dosages of other analgesic medications in conjunction with their primary physician. Analgesic medication use and doses will be tracked at the above time points to assess changes over time. Semistructured interviews will be conducted at 2 points within the study period: at weeks 1 and 20 and after the ketamine infusions (Table 1). The interviews will be audio-recorded to ensure the responses are accurately captured. In-person interviews will be recorded with an encrypted device, and phone interviews will be recorded through the Unity Health Zoom (Zoom Video Communications Inc) recording option. The audio recording files will be saved on St. Michael’s Hospital secure and restricted servers, and the files will be labeled by the study number. The recordings will be transcribed by the research team, and after verifying that the transcriptions are accurate, the audio recordings will be destroyed. Questionnaires will be delivered to patients at prespecified time points, as outlined in the study timeline below.

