**Figure 1 figure1:**
[figure not shown]
Overview of study design with primary and secondary outcomes. CBT/MM: cognitive behavior therapy/mindfulness and meditation.

**Table 1 table1:** Study timeline from weeks 1-20.

Time point		Screening	Week 1	Week 2	Week 7	Week 12	Week 16	Week 20
		Visit 1	Visit 2	Visit 3	Visit 4	Visit 5	Visit 6	Visit 7

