### Follow-Up Data

In all arms, at each follow-up visit, participants will complete the PROMIS-PI scale, PCS, PHQ-9, GAD-7, and the PGIC to assess outcome measurements. Follow-ups will be conducted every 4 weeks over the phone to maintain the blindness of the research team.

For females, a urine pregnancy test will be required for those randomized to the ketamine-hydrochloride infusion alone or the ketamine-hydrochloride infusion+CBT/MM arms in order to confirm that the patient is not pregnant before each ketamine infusion treatment.

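### The missing-data feasibility criterion is set at one month without saying from when, and the readings lead to different visits and possibly different results

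*Protocol article*

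**What the plan says.** Protocol article, Primary Outcome, lists six feasibility outcomes. One is the "Percentage of patients with incomplete pain intensity and pain interference data at 1 month and stated or ascribed reason", with a limit of under 10%. The Hypothesis section repeats it as the "percentage of patients with incomplete pain intensity and pain interference data at 1 month" and ends it with "loss to follow up, or missing data; 3/30, <10" per cent. Neither section gives a starting point for the month. Primary Outcome says of the cutoffs that they "will help determine whether protocol changes are required before proceeding with a definitive trial".

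The schedule is given in three places:

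- Table 1 ("Study timeline from weeks 1-20") has questionnaires at weeks 1, 2, 7, 12, 16 and 20.
- Secondary Outcome agrees: "Scores for all outcomes at weeks 2, 7, 12, 16, and 20 will be compared to baseline scores". It gives the main clinical time point as "pain intensity and pain interference at week 20 (4 weeks post-completion of treatment; Figure 1".
- Follow-Up Data has a different rhythm: "Follow-ups will be conducted every 4 weeks over the phone to maintain the blindness of the research team". It has the questionnaires completed at each follow-up visit.

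Pain intensity on the 0-10 Numeric Rating Scale is named in Secondary Outcome. It is missing from the questionnaire row of Table 1 and from the instrument lists in Baseline Data and Follow-Up Data.

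**The concern.** A progression criterion should point to one visit, fixed before any data are seen. This one does not, and the schedule does not settle it. No Table 1 visit falls between weeks 2 and 7, where a month from baseline or from the first infusion would lie. A month after treatment does reach a scheduled visit, but which one depends on when treatment is taken to end in Arm 1.

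Incomplete data build up as people withdraw, so an early visit is easier to pass than week 20. If the visit is chosen once the data are in, the result on a primary outcome may depend on that choice. An early reading would also say little about completeness at week 20, which is where the pain outcomes are to be judged.

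**Working it through.** **1. The stated cutoff.** The Hypothesis section pairs 3/30 with under 10%. 3/30 = 10.0%, which is not below 10%. The largest count that passes is 2/30 = 6.7%.

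**2. Where one month falls.** Inputs: baseline at week 1 (Baseline Data), infusions at weeks 2, 7 and 12 and therapy to week 16 (Abstract, Table 1), and the Table 1 visits. One month is taken as 4 weeks.

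| Counted from | Target | Nearest Table 1 visit | Gap |
|---|---|---|---|
| Baseline, week 1 | 1 + 4 = week 5 | week 7 | 2 weeks |
| First infusion, week 2 | 2 + 4 = week 6 | week 7 | 1 week |
| Last infusion, week 12 (Arm 1) | 12 + 4 = week 16 | week 16 | 0 |
| End of therapy, week 16 | 16 + 4 = week 20 | week 20 | 0 |

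With a month of 30.4 days the gaps are 1.66, 0.66, 0.34 and 0.34 weeks, and the nearest visits are the same. At week 20, Arm 1 is 20 - 12 = 8 weeks past its last infusion, while Arms 2 and 3 are 20 - 16 = 4 weeks past the end of therapy.

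**3. The four-weekly follow-ups.** Calendar weeks 4, 8, 12, 16 and 20 agree with Table 1 only at 12, 16 and 20. Counted from week 1 (5, 9, 13, 17, 21) they agree at none.

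**4. Can the choice of visit change the result?** Under 20% withdrawal allows at most 5/30 = 16.7%. (The Hypothesis section prints 6/30, but that is exactly 20%.) The missing-data criterion counts withdrawal as a reason for incomplete data, and Withdrawal Criteria ends data collection the day after withdrawal. With no other missing data:

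| Withdrawals before week 20 | Share | Under 20% withdrawal | Under 10% incomplete at week 20 |
|---|---|---|---|
| 3 | 10.0% | met | missed |
| 4 | 13.3% | met | missed |
| 5 | 16.7% | met | missed |

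At an early visit the same trial passes if no more than 2 of these people have left by then.

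**5. Sensitivity of the pass probability.** The protocol gives no expected rate of incomplete data at any visit, so the rates here are assumptions. With X binomial (30, p):

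| Assumed true rate p | P(X ≤ 2) | P(X ≤ 3) |
|---|---|---|
| 5% | 0.81 | 0.94 |
| 10% | 0.41 | 0.65 |
| 15% | 0.15 | 0.32 |
| 20% | 0.04 | 0.12 |

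The chance of passing falls steeply as incompleteness rises, so a visit with fewer losses is a materially easier test. The two columns also show that reading the cutoff as 2 or as 3 of 30 matters.

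**6. The pain intensity half.** Secondary Outcome intends scores for all its outcomes at weeks 2 to 20, so collection of the rating scale is implied. The schedule lists do not show it at any visit.

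**The case against.** The strongest reply is that the meaning can be recovered. Secondary Outcome places the same two measures at week 20 and describes that as four weeks after treatment, for all arms together. Even if Arm 1 is counted from week 12, the result is week 16, which is also a questionnaire visit. Follow-Up Data implies a contact near week 4 or 5. This stands against the stronger reading a reader might take from Table 1: that no assessment exists at one month, so the criterion cannot be evaluated or all 30 participants would count as incomplete. The documents do not support that, and data never scheduled are not incomplete data. Nor does any starting point put one month at week 2. What the reply does not do is show which reading is meant: neither statement of the criterion ties the month to the end of treatment.

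A second reply is that other criteria guard retention. The withdrawal limit has no one-month restriction. Adherence above 90% needs at least 28 of 30 completing all visits on a strict reading (27/30 = 90%), so three people leaving during treatment would already miss a target. This stands and limits the damage. It does not cover people lost after their last treatment visit, and the protocol's own printed 27/30 would let three non-completers through.

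Third, the decision is graded: missing one threshold may lead to modification and does not by itself stop the definitive trial. That also stands, and it lowers the importance. Figure 1, cited for the week 20 time point, is not available here and may show the starting point; the two statements of the criterion would still need to say it.

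**Conclusion.** The point holds as an ambiguity in a primary feasibility criterion. One month has no starting point. Two natural readings meet no Table 1 visit, the end-of-treatment reading gives week 20 or, for Arm 1, possibly week 16, and Follow-Up Data conflicts with Table 1. The result can depend on the reading: 3 to 5 withdrawals of 30 pass the withdrawal limit and fail the missing-data limit at week 20, yet could pass it at an early visit. That rests on some of those withdrawals coming after the early visit and on few other missing data. If withdrawal stays under 10%, as the Hypothesis section expects, withdrawal alone would not produce the conflict.

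The printed 3/30 against under 10% is a separate, certain error of one participant. Importance is moderate: the wording should be settled before recruitment, but the criterion is not unusable.

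**What to change.** In Primary Outcome and Hypothesis, replace the one-month time point with week 20 for all arms, so that the criterion refers to the visit of the main pain outcomes. State the cutoff as at most 2 of 30 and correct the 3/30 in Hypothesis. Reconcile the four-weekly follow-ups in Follow-Up Data with the Table 1 weeks. Add the pain intensity Numeric Rating Scale to the questionnaire row of Table 1 and to the lists in Baseline Data and Follow-Up Data. If the sponsor prefers another week, it should be named with its starting point before any data are seen.

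The cost is wording only, since the article reports that recruitment had not begun by 1 November 2023. The criterion may be harder to meet than under an early reading. If week 20 was already meant, the timing change only clarifies.

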#### Secondary Outcome

The secondary outcomes chosen for the definitive trial follow consensus recommendations of core domains that should be addressed in studies examining chronic pain. Information will be collected in these domains as part of the pilot trial using survey-based outcome assessments, either in person during study visits or over the telephone by trained research personnel. The following pain score questionnaires will be used:

Pain intensity on an 11-point (0-10) Numeric Rating Scale.Pain interference on the Patient-Reported Outcomes Measurement Information System (PROMIS-PI) scale.Catastrophic thinking about pain, as measured by the Pain Catastrophizing Scale (PCS).Features of depression, as measured by the Patient Health Questionnaire-9 (PHQ-9).Features of anxiety, as measured by the Generalized Anxiety Disorder-7 (GAD-7).Patient Global Impression of Change Scale (PGIC).

Secondary clinical outcomes will include changes relative to baseline assessment in pain intensity and pain interference at week 20 (4 weeks post-completion of treatment; Figure 1). Scores for all outcomes at weeks 2, 7, 12, 16, and 20 will be compared to baseline scores to assess any progressive additive effects between the treatments. For any patients who withdraw before week 20, their last documented responses will be used as a comparison against baseline data. Patients will be allowed to adjust the dosages of other analgesic medications in conjunction with their primary physician. Analgesic medication use and doses will be tracked at the above time points to assess changes over time. Semistructured interviews will be conducted at 2 points within the study period: at weeks 1 and 20 and after the ketamine infusions (Table 1). The interviews will be audio-recorded to ensure the responses are accurately captured. In-person interviews will be recorded with an encrypted device, and phone interviews will be recorded through the Unity Health Zoom (Zoom Video Communications Inc) recording option. The audio recording files will be saved on St. Michael’s Hospital secure and restricted servers, and the files will be labeled by the study number. The recordings will be transcribed by the research team, and after verifying that the transcriptions are accurate, the audio recordings will be destroyed. Questionnaires will be delivered to patients at prespecified time points, as outlined in the study timeline below.

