**Objective:**

The primary objective of this study is to examine the feasibility of a parallel 3-arm pilot randomized controlled trial whereby patients are randomized to either intravenous ketamine alone, cognitive behavioral therapy (CBT) and mindfulness meditation (MM) training (CBT/MM), or the combination of intravenous ketamine and CBT/MM. The secondary outcome is to assess the durability and efficacy of combination intravenous ketamine and CBT/MM for treatment of chronic pain as compared to CBT/MM or intravenous ketamine alone (assessed at week 20 of the study).

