**Methods:**

This is a single-center, 16-week, 3-arm pilot study that will take place at the Chronic Pain Clinic at St. Michael’s Hospital, Toronto, Ontario, which receives 1000 referrals per year. Patients will be enrolled in the study for a total of 20 weeks. Participants who are allocated CBT/MM therapy will receive remote weekly psychotherapy from week 1 to week 16, inclusive of health coaching administered through the NexJ Health Inc (NexJ Health) platform. Patients who are allocated ketamine-infusion therapy will receive monthly ketamine infusion treatments on weeks 2, 7, and 12. Patients who are allocated ketamine+CBT/MM will receive weekly psychotherapy from weeks 1 to 16, inclusive, as well as ketamine infusion treatments on weeks 2, 7, and 12. We will be assessing recruitment rates, consent rates, withdrawal rates, adherence, missing data, and adverse events as pilot outcome measures. Secondary clinical outcomes include changes relative to baseline in pain intensity and pain interference.

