### Withdrawal Criteria

A participant will be withdrawn if the participant presents with a severe adverse event or unknown allergic reaction during the first administration of ketamine-hydrochloride or if the participant wants to withdraw from the study for any reason. The participant will receive the necessary treatment to alleviate any untoward events and will be monitored by the study physician until judged appropriate for discharge. Participants will be followed up on the following day to ascertain more details on their condition. Data from a participant who has been withdrawn will be collected up to the day following their withdrawal to ensure that the participant has no more complications. If a participant withdraws from the study at any time, the reasons for withdrawal will be collected and documented as a feasibility study outcome.

Since this is a feasibility study without a specific sample size required to analyze any outcome, participants will not be replaced or added.

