### Outcome Analysis

Based on the primary end points, we will determine whether or not this pilot study is as follows:

Feasible: all feasibility outcomes are met; no protocol modifications are needed,Feasible with modification: all feasibility outcomes are met or can be met with protocol modifications, andNot feasible: Even with protocol modifications, some feasibility outcomes cannot be met.

In terms of statistical analyses for this feasibility study, preliminary analyses will consist of univariate tests to compare clinical and demographic variables of interest. Linear regression analysis will be used to quantify the strength and magnitude of the relationship between the intervention and the coprimary outcomes. Secondary outcomes will be analyzed as continuous measures using generalized linear regression models.

For any missing data where patients do not attend the allocated sessions or do not complete all components of the relevant questionnaires, this will be noted and documented to assess the overall feasibility of this study. Data will not be extrapolated or interpreted for these missing data sets.

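### For patients who withdraw before week 20 the protocol states two conflicting missing-data rules, and the carry-forward rule could bias the week-20 durability estimate in either direction

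*Protocol article*

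**What the plan says.** Three statements in the protocol article bear on a patient who leaves early.

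- Secondary Outcome: "For any patients who withdraw before week 20, their last documented responses will be used as a comparison against baseline data".
- Outcome Analysis: the rule opens with "For any missing data where patients do not attend the allocated sessions or do not complete all components of the relevant questionnaires", says that such gaps will be recorded as feasibility information, and ends: "Data will not be extrapolated or interpreted for these missing data sets".
- Withdrawal Criteria: "Data from a participant who has been withdrawn will be collected up to the day following their withdrawal".

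The endpoint concerned is "changes relative to baseline assessment in pain intensity and pain interference at week 20 (4 weeks post-completion of treatment"). The abstract gives its purpose: "The secondary outcome is to assess the durability and efficacy of combination intravenous ketamine and CBT/MM for treatment of chronic pain", compared with either treatment alone at week 20. The combination arm receives "weekly psychotherapy from weeks 1 to 16, inclusive, as well as ketamine infusion treatments on weeks 2, 7, and 12"; the ketamine-alone arm has the same infusion weeks. Scores are taken at weeks 2, 7, 12, 16 and 20. The Introduction reports that ketamine's benefit has not lasted under any infusion regimen studied.

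**The concern.** For a withdrawn patient, one rule supplies a week-20 value and the other forbids it. With no order of precedence, an analyst could defend either and could choose after seeing the data.

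The carry-forward rule is also hard to defend for this endpoint. Week 20 is 4 weeks after psychotherapy ends and 8 weeks after the last infusion (20 - 12 = 8). It was placed there to see whether benefit lasts. Carrying an earlier score to that date assumes, for that patient, no change over the period in question. Treating the carried value as observed also understates uncertainty.

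Withdrawal may differ by arm. One stated trigger, a severe adverse event or allergic reaction at the first infusion, can occur only in the two ketamine arms.

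The clinical comparison is secondary, but the Discussion says that the results will help set the sample size of the definitive trial. A distorted effect or variance could be carried into that calculation.

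**Working it through.** **Do the rules overlap?**

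1. The carry-forward rule covers everyone who withdraws before week 20.
2. The no-extrapolation rule covers missed sessions and incomplete questionnaires. It neither names nor excludes withdrawal.
3. Because collection stops the day after withdrawal, a withdrawn patient has no week-20 questionnaire and so meets the second description too.
4. Primary Outcome treats withdrawal as one cause of incomplete pain data at 1 month: "withdrawal due to side effects, loss of follow-up, or missing data; <10"%.
5. No sentence says which rule prevails. The overlap is confined to withdrawn patients; for those still in the study only the no-extrapolation rule applies.

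**What could carry-forward do to the estimate?** The protocol gives no figure to reproduce, so this is an illustration.

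Inputs from the protocol:
- 30 patients in total (Aim).
- Withdrawal expected below 10%, with a feasibility limit of 20% (Hypothesis, Primary Outcome).
- Reduction of 25% to 43% on ketamine versus control (Introduction).

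Assumptions:
- 10 patients per arm (the allocation ratio is not stated).
- Baseline Numeric Rating Scale (NRS) score of 6.
- The last score before withdrawal shows the full reduction, and the true week-20 change is zero.

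Formula: bias in an arm's mean change = f x (change at last score - true change at week 20), where f is the share of the arm withdrawn.

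- On-treatment reduction: 6 x 0.25 = 1.50; 6 x 0.43 = 2.58 points.
- f = 0.1: 0.1 x 1.50 = 0.15; 0.1 x 2.58 = 0.26.
- f = 0.2: 0.2 x 1.50 = 0.30; 0.2 x 2.58 = 0.52.

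With other baselines:

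| Baseline NRS | f = 0.1 | f = 0.2 |
|---|---|---|
| 4 | 0.10-0.17 | 0.20-0.34 |
| 6 | 0.15-0.26 | 0.30-0.52 |
| 8 | 0.20-0.34 | 0.40-0.69 |

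The opposite direction: if the true week-20 reduction is 2.58 and 20% leave at the first infusion with a last score equal to baseline, the arm shows 0.8 x 2.58 = 2.06, so the effect is understated by 0.52.

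**Contrast of combination (arm 3) minus ketamine alone (arm 1).** Positive means a larger reduction in arm 3. If neither effect lasts, bias = (f3 - f1) x 2.58.

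- Equal withdrawal in both arms: 0.
- 20% in arm 3 only: +0.52.
- 20% in arm 1 only: -0.52.

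If instead arm 3 is truly durable, arm 1 is not, and 20% leave arm 1, the contrast falls from 2.58 to 2.58 - 0.52 = 2.06. Here carry-forward hides part of a real advantage.

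**The case against.** **The rules might be read as separate.** One can be taken to govern those who withdraw and the other those who stay but miss a visit. On that reading both can be followed, and it may be what was meant. It limits the conflict to withdrawn patients but does not remove it, because the no-extrapolation text makes no exception for them.

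**A reader might infer that carry-forward would manufacture durability.** The documents do not support this. Durability is judged as combination versus either treatment alone, and that contrast can be inflated, unchanged or reduced. Patients who leave at the first infusion would tend to carry near-baseline scores, which works against the ketamine arms. Week 16 is also an assessment visit, and in the ketamine-alone arm it already falls 4 weeks after the last infusion. Nor does the article say whether infusion-day questionnaires precede the infusion. A carried score therefore need not reflect peak benefit.

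**The size is modest and the outcome secondary.** With 10 per arm and an assumed SD of 1.5-2.5 points, the standard error of a two-arm difference is SD x sqrt(2/10) = 0.67-1.12, more than the biases shown. The protocol states that it is not powered for these effects, and no feasibility criterion uses a carried score. This stands, and it lowers the severity.

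**The alternative model has assumptions of its own.** A likelihood-based analysis relies on data missing at random. For early adverse-event withdrawals it draws on patients who tolerated ketamine, and so may flatter that arm. This also stands; the assumption should be stated.

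**Conclusion.** The point holds in a limited form. For patients who withdraw before week 20, Secondary Outcome and Outcome Analysis conflict, and Withdrawal Criteria ensures that these patients have no week-20 score. Carry-forward is a poor rule for an endpoint measured after treatment ends, and it could bias the durability estimate either way.

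Under the assumptions above, with a baseline of 6, the within-arm bias is 0.15-0.26 NRS points at 10% withdrawal and 0.30-0.52 at 20%. The bias in the combination-minus-ketamine contrast runs from about -0.52 through 0 to +0.52. The size depends on the assumed baseline, arm size and complete loss of effect.

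This should be fixed, but it does not threaten the trial's main purpose: the feasibility decision does not depend on it. The reason to act is that the results feed the planning of the definitive trial.

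**What to change.** 1. Delete the carry-forward sentence in Secondary Outcome, so that one rule covers withdrawn patients and agrees with Outcome Analysis.
2. Analyse all observed scores at weeks 2 to 20 with a likelihood-based repeated-measures model with arm, week and arm-by-week terms, adjusted for the baseline score. State the missing-at-random assumption, and use a simple covariance structure suited to about 30 patients.
3. Keep carry-forward, if at all, as a labelled sensitivity analysis.
4. In Withdrawal Criteria, separate ending study treatment from withdrawing consent for data collection. For patients who end treatment but still consent, continue the telephone questionnaires to week 20. This concerns data collection only and leaves the criteria for ending treatment as they are.

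The cost is protocol wording, a few more telephone questionnaires and a slightly more complex model. Telephone assessment is already planned, and recruitment had not begun at the article's status date of November 1, 2023.
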